
#### Sample Size

We assumed 85% clinical recovery in the group assigned to the full antibiotic course based on some studies [12,42-44]. Considering a power of 80%, a level of significance of 5%, one-sided noninferiority margin of 10%, as recommended by the guideline on the evaluation of medicinal products indicated for treatment of bacterial infections issued by the European Medicines Agency in 2022 [45], which gave a sample size of 402 patients. Assuming that the primary outcome could not be evaluated in 15% of patients, 474 patients needed to be included in the study (237 in the control group and 237 in the intervention group).

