#### Assignment of Interventions: Allocation

##### Sequence Generation

Patients fulfilling the inclusion criteria will be asked to participate in the trial. All patients who agree to participate and provide signed informed consent will receive an increasing sequential patient number and be randomly assigned to one of the 2 treatment groups in a 1:1 ratio stratified per main diagnosis, one for acute rhinosinusitis and another one for lower RTI.

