### Statistical Methods

Statistical methods for primary and secondary outcomes: The characteristics of the study population will be described using frequencies for categorical variables and mean and SD for quantitative variables. To compare the clinical efficacy between the 2 strategies, we will analyze the difference in the proportion of recovered patients in each arm on day 14. Efficacy evaluation will be primarily based on intention-to-treat analysis in such a way that any event in any patient will be included in the group to which the patient was randomized, and per protocol analysis will be used as a secondary analysis. For all analyses, the level of significance will be *P*<.05.

Interim analyses: No interim analysis is planned.Methods for additional analyses (eg, subgroup analyses): We will conduct subgroup analyses of the primary outcome of participants with lower RTIs, and for acute rhinosinusitis.

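### The two diagnosis subgroups come under the general P<.05 rule, with no comparison between diagnoses named, in a trial sized only for the overall result

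*Protocol article*

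**What the plan says.** - **Randomization** (Sequence Generation): 1:1 and "stratified per main diagnosis, one for acute rhinosinusitis and another one for lower RTI".
- **Main comparison** (Statistical Methods): "we will analyze the difference in the proportion of recovered patients in each arm on day 14". The section does not say whether the estimate is stratified or adjusted.
- **Subgroups** (Statistical Methods, under additional analyses): "We will conduct subgroup analyses of the primary outcome of participants with lower RTIs, and for acute rhinosinusitis".
- **Significance** (Statistical Methods): "For all analyses, the level of significance will be" P<.05. Subgroups are not exempted and sidedness is not given.
- **Size** (Sample Size): "We assumed 85% clinical recovery in the group assigned to the full antibiotic course based on some studies", and "Considering a power of 80%, a level of significance of 5%, one-sided noninferiority margin of 10" percent. This gives 402 evaluable patients, or 474 after allowing for 15% not evaluable.

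The article gives no expected split between lower RTI and rhinosinusitis, no margin for a subgroup, and no rule for reading a subgroup result. The primary objective concerns the two diagnoses together.

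**The concern.** Readers will ask whether stopping early works as well in rhinosinusitis as in lower RTI. Two separate analyses do not answer that, because a result that is convincing in one diagnosis and not in the other is not evidence that the effects differ. Only a comparison of the two effects addresses the question, and none is named.

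The one decision rule that the text supplies for these analyses is P<.05. In a noninferiority trial with a single stated margin, a reader or analyst could easily apply that margin within each diagnosis. Each diagnosis has far fewer patients than the margin was powered for, so an inconclusive result in one of them could be taken for an exception to the overall finding. The trial is open-label, and the Blinding section says that blinding the data analysts is also difficult. A reading rule chosen after the results are seen would be hard to defend.

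**Working it through.** **Inputs from the article:** 85% resolution (taken in both arms, so nothing truly differs), margin 10 points, power 80%, 402 evaluable (201 per arm), 474 enrolled (237 per arm). **Assumption:** diagnosis splits of 50:50, 70:30 and 80:20, because none is stated.

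**Reproducing the plan's figure.** n per arm = (1.96 + 0.8416)² × 2 × 0.85 × 0.15 / 0.10² = 7.849 × 0.255 / 0.01 = 200.1, rounded up to 201, so 402. Then 201/0.85 = 236.5, rounded up to 237 per arm, so 474. One-sided 5% would give 158 per arm (316). The stated 402 therefore corresponds to one-sided 2.5%, although the article writes "a level of significance of 5%, one-sided noninferiority margin of 10" percent. Both levels are shown below.

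**Power within a diagnosis.** Power = Φ(0.10 / √(0.255/n) − z), where n is patients per arm in that diagnosis and z is 1.96 or 1.645. Example: n = 100.5 gives SE 0.0504, and Φ(1.985 − 1.96) = 0.51. The two diagnoses are independent, so P(at least one fails) = 1 − power₁ × power₂.

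| Split | n per arm | Power, one-sided 2.5% | At least one fails, 2.5% | At least one fails, 5% |
|---|---|---|---|---|
| 50:50 | 100.5 / 100.5 | 51% / 51% | 74% | 60% |
| 70:30 | 140.7 / 60.3 | 65% / 34% | 78% | 65% |
| 80:20 | 160.8 / 40.2 | 71% / 24% | 83% | 72% |

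Simulation with 400,000 replicates gave 73%, 77% and 81% at one-sided 2.5%. Among simulated trials that did show noninferiority overall, the figures were 67%, 71% and 76%.

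**Sensitivity.**
- All 474 evaluable: 67% to 79% (one-sided 2.5%) or 52% to 67% (one-sided 5%) over the same splits.
- 90% resolution, 50:50 split: 57% or 42%.
- 95% resolution, 50:50 split: 19% or 11%.
- If P<.05 means a test of difference in each diagnosis, the chance of at least one false positive is 1 − 0.95² = 9.75%.

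**Interaction instead.** With identical arms, a two-sided 5% interaction test flags a difference in 5.2% to 5.5% of simulated trials. Its 95% half-width is 1.96 × √(0.255/n₁ + 0.255/n₂): 14.0 points at 50:50, 15.2 at 70:30 and 17.5 at 80:20.

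**Main comparison, stratified or not** (50:50 split, one-sided 2.5%, simulated power):

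| Resolution in the two diagnoses | Unstratified | Stratified |
|---|---|---|
| 85% and 85% | 80.2% | 80.3% |
| 80% and 90% | 80.5% | 81.2% |
| 75% and 95% | 81.2% | 83.5% |

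The rates in the last row imply a stratified SE of √((0.75 × 0.25 + 0.95 × 0.05)/201) = 0.0342, against the unstratified √(0.255/201) = 0.0356. The unstratified interval is slightly too wide, which is conservative.

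**The case against.** The article never says that noninferiority will be declared or rejected within a diagnosis. The margin appears only in the overall sample size, no subgroup objective is listed, and the subgroups stand under additional analyses. P<.05 for all analyses does not exclude an interaction test, and the analysis plan, which is not shown, may contain one. All of this stands, and it makes the 74% to 83% conditional. It does not remove the point: the published text gives one significance rule for everything, subgroups included, and leaves it unqualified.

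A further objection is that the remedy changes labels more than numbers. A 95% CI for one diagnosis will cross −10 points exactly as often as the one-sided 2.5% test fails, and the interaction is too imprecise to establish equal effects. That is correct. The gain is that an inconclusive interval is no longer presented as a verdict, and that the between-diagnosis question gets an estimate of its own.

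A reader might also infer that the main comparison ignores the strata and that this produces the subgroup failures. The documents do not support either step. A stratified estimate is also a difference in proportions, and silence about adjustment is normal when the analysis plan is a separate document. The subgroup failures come from small numbers within each diagnosis, whatever is done in the main analysis.

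**Conclusion.** The point holds as a limited one about wording and method. Separate analyses by diagnosis under a blanket P<.05, with no comparison of effects named, invite a reading that the trial is not sized to support. If each diagnosis were held to the 10-point margin, at least one would fail to show noninferiority in about 74% to 83% of trials with identical arms (60% to 72% at one-sided 5%). This rests on 85% resolution, 402 evaluable patients and assumed splits of 50:50 to 80:20, and it is lower at higher resolution rates.

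It would go too far to say that the plan as written makes a spurious exception likely. No verdict per diagnosis is stated, and an inconclusive subgroup reflects low power (type II error), not a false signal. The primary conclusion is unaffected: an unstratified main comparison would be valid and slightly conservative, at a cost of about 0.1 to 2 points of power.

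**What to change.** 1. State that lower RTI and rhinosinusitis results are descriptive: a risk difference with 95% CI for each, exempt from the P<.05 rule and without a noninferiority verdict.
2. Assess heterogeneity by a treatment-by-diagnosis interaction on the risk-difference scale, reported with its 95% CI. Say in advance that it is imprecise (half-width about 14 to 15 points for splits up to 70:30, wider if more uneven), so that a null result is not read as proof of equal effects.
3. Separately, estimate the primary risk difference stratified by diagnosis, for example with Mantel-Haenszel weights, with its 95% CI. The gain is small and costs nothing.

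These are wording changes only, since diagnosis is recorded at randomization. The price is that no formal claim can be made for one diagnosis alone. Powering both at 80% would take about 804 evaluable patients (2 × 402) with an equal split, or 946 enrolled (804/0.85).

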### Cost-Effectiveness Analyses

We will estimate the cost-effectiveness of tailoring antibiotic duration therapy for the “within-trial” period (28 days) and over the expected lifetime of patients (lifetime/long-run model).

In the within-trial analysis, cost-effectiveness will be measured by the incremental cost per patient achieving clinical resolution. In this analysis, effectiveness will be calculated using the primary endpoint of the study. Costs considered will include antibiotic prescription costs according to the duration of treatment, other drug costs, reconsultations in primary and secondary care (including hospitalizations), and costs associated with adverse events. Data on health care resource use and duration will be taken from the patients’ diaries, from the collected information in the e-CRF, and at the follow-up phone calls at days 14 and 28, and from a review of patients’ medical notes. Unit cost data will be taken primarily from national sources published by the Spanish Ministry of Health. The incremental cost-effectiveness ratio will be calculated by dividing the estimated difference in costs by the estimated differences, in effects observed between the intervention and control groups. Nonparametric methods to calculate confidence intervals around the incremental cost-effectiveness ratio based on bootstrapped estimates of the mean cost and effect differences will be used.

The intervention under evaluation in this study is likely to have an impact beyond the trial period. To capture these potential effects, we will extrapolate the results to an extended time horizon, that is, considering the remaining life expectancy of the patients. In this analysis, we will complement data from the trial with relevant data from the published literature to estimate the incremental cost per quality-adjusted life year (QALY) gained. Health-related quality of life data collected during the trial using the EQ-5D-5L questionnaire at baseline, at 14 and 28 days will be used as inputs to estimate baseline QALY values for this patient group. A decision-analytical model synthesizing all relevant information will be used to estimate the differences in lifetime QALYs and lifetime health care costs of a cohort of patients under the tailored duration strategy versus the standard of care strategy.

### Methods in Analysis to Handle Protocol Nonadherence and Any Statistical Methods to Handle Missing Data

Analyses will be performed as intention to treat (pragmatic trial) and also per protocol. The primary analysis population will comprise all participants, irrespective of follow-up.

Data will be examined for missing values and outliers. Measures of central tendency and dispersion for continuous study parameters will be portrayed. Extreme or unexpected values will be examined individually for authenticity, and data discrepancies addressed where appropriate.

### Plans to Give Access to the Full Protocol, Participant-Level Data, and Statistical Code

The full protocol, statistical code, and e-CRF templates designed for the study will be available upon request once the report has been published. Participant-level data will not be available.

## Results

Recruitment of patients will start in October 2025 and will be stopped in April 2027. The current protocol is version 3 of July 31, 2025.

## Discussion

### Principal Findings

The limited to moderate impact in reducing unnecessary antibiotic use in primary care observed in antimicrobial stewardship programs necessitates the exploration of new strategies aimed at reducing patients’ exposure to unnecessary courses [30]. This highlights the need for exploring new strategies to minimize patients’ exposure to unnecessary antibiotic courses. Convincing doctors, especially GPs, not to prescribe antibiotics when uncertain or under patient pressure is challenging. Despite the widespread practice, standard durations for common infections lack support from clinical studies [7]. However, recent randomized clinical trials, conducted mainly in the last 2 decades, show that ending antibiotic courses by day 2-3 for most RTIs is effective and safe, similar to early studies on short-term antibiotic courses for uncomplicated urinary tract infections carried out 20 years ago [47]. We believe health care professionals should encourage patients to stop antibiotic treatment promptly after symptom resolution unless a serious infection is suspected. In our clinical trial, these potential serious infections are clearly excluded. Continuing antibiotics beyond symptom resolution does not appear to prevent or reduce AMR. Conversely, reducing the duration of courses has been shown to curb the spread of AMR in pneumonia. It is essential to move away from strict, predetermined durations and adopt a patient-centered approach by customizing antibiotic courses to meet each patient’s individual needs. The key challenge involves identifying when exactly antibiotics can be safely stopped based on symptoms to minimize the chances of relapse. We currently lack evidence on how pathogen burden is associated with symptoms experienced by patients with RTIs.

STORM’s main focus on primary care settings makes it directly applicable to the daily practice of GPs who frequently encounter patients with uncomplicated RTIs. Infectious diseases represent one-third of all GP consultations, with over half of these visits attributed to RTIs [48]. This indicates that RTIs are among the most prevalent conditions encountered by GPs in their clinical practice. It acknowledges the challenges faced by health care professionals, particularly GPs, in resisting patient pressure and uncertainty when deciding whether to prescribe antibiotics. By advocating for a patient-centered approach to antibiotic prescribing, the proposal provides practical guidance for health care providers to tailor treatment regimens according to individual patient needs and clinical circumstances [49]. STORM draws upon recent clinical trials conducted over the past 2 decades, suggesting that the findings are based on contemporary evidence and thus likely applicable to current clinical practice.

To the best of our knowledge, there has not been any study in primary care exploring the feasibility and efficacy of stopping the antibiotic course once the clinical signs of the patient have improved and the CRP level is low. Furthermore, a randomized clinical trial has never been conducted to assess the effectiveness and safety of this crucial strategy in combating AMR and drug-related adverse events. Primary health centers are the first contact point for patients with RTI symptoms, which is why we will conduct the study in this setting. This will constitute the first clinical trial aimed at answering whether it is safe to shorten and tailor the antibiotic therapy duration to the needs of the patients. This study does not pursue the medicalization of tailoring the antibiotic course by requiring patients assigned to the intervention group to return for a clinical reassessment and CRP testing; however, this is the first trial of its kind. We aim to determine the efficacy and safety of this strategy. If tailoring antibiotic courses for RTIs proves to be as effective and safe as completing the entire course, further studies will investigate the necessity of the reassessment visit.

### Limitations

This is a pragmatic clinical trial evaluating the efficacy of different antibiotic therapy durations for acute RTIs, and therefore, masking techniques are not used. One limitation of this study is that a percentage of self-limiting viral infections will be included. While antibiotics are not the recommended treatment, they are still frequently prescribed for most RTIs worldwide [3]. However, all participants will receive a summary of the updated current guidelines, which discourage the use of antibiotics for most patients with acute rhinosinusitis, uncomplicated acute bronchitis, and acute COPD exacerbations without purulent sputum, leaving the decision to the clinician in this pragmatic approach. Nevertheless, we believe that the percentage of “viral self-limiting infections” included in this randomized clinical trial will be much lower than what is typically observed under normal conditions, as GPs will be informed about the appropriate indications for therapy and will have this information available before deciding whether to prescribe a β-lactam to the participant.

Both the primary and some of the secondary objectives of the study are based on information provided by the patients themselves. Regarding the CRP rapid testing, we are aware that high CRP levels can signal systemic inflammation in conditions like inflammatory disorders, not just infections. There is limited research on how CRP changes day by day in RTIs. Although levels above 100 mg/L might reflect the natural progression, we set conservative thresholds for this initial trial on shortening treatments as patients improve. Some centers are only open on weekdays, from Monday to Friday. In these cases, if a patient feels better over the weekend, they will need to wait until the following Monday to be assessed. To minimize this limitation, we will recruit only centers that remain open on Saturdays or, preferably, those that provide out-of-hours services. This strategy aims to ensure timely follow-up and reduce delays in clinical assessment.

The concept of “feeling better” is inherently subjective and can vary significantly across individuals, types of infections, and symptom profiles [50]. For some patients, it may indicate partial symptom improvement, while for others it may imply complete resolution of all symptoms. Certain symptoms, such as fever, might be a more reliable indicator for clinical improvement and the safe discontinuation of antibiotics, whereas symptoms like cough may persist longer without significantly impairing daily functioning. Additionally, some patients with RTIs may prefer to stop antibiotics only after full symptom resolution, while others may find the notion of symptom improvement too ambiguous, leading to uncertainty about when to discontinue treatment. To address this challenge, our study defines the appropriate time to stop antibiotic treatment based on a combination of clinical and patient-reported criteria: overall symptom improvement as reported by the patient, normalization of key vital signs—particularly body temperature, and the absence of elevated inflammatory markers, specifically CRP. As a pragmatic randomized clinical trial, this study is designed to provide real-world evidence on how patients interpret and respond to the concept of “feeling better” in the context of antibiotic use. Furthermore, to enhance our understanding, we will conduct a qualitative study with a subset of patients in the intervention group to explore their perceptions and experiences related to symptom improvement and treatment decisions. Insights from this qualitative component will help refine a more practical and clinically applicable definition of when it is appropriate to discontinue antibiotic therapy, ultimately supporting clinicians in providing more precise and consistent advice.

As with any randomized clinical trial, the STORM study faces some challenges. One potential difficulty is recruiting enough patients with acute RTIs who are willing to participate. Despite this moderate risk, the study is planned to run from October 2025 to April 2027, covering 2 winter periods, with the last patient recruited by March 2027. To ensure recruitment success, tight follow-up processes and various strategies will be implemented. These strategies may include inviting other professionals from existing centers to participate, extending the recruitment period by an additional 2 months if needed, and, if necessary, opening recruitment at additional sites to increase the pool of candidates. In addition, to minimize inclusion bias, consecutive recruitment of patients who meet the inclusion criteria and do not meet any exclusion criteria will be encouraged [51].

Professionals will follow up with all patients assigned to the intervention group on day 3 for assessment of the clinical condition and as a reminder to reach out to the center as they feel better. Professionals will be trained on how to explain the study’s objectives and the importance of adhering to the study procedures. For patients who do not return their symptom diaries, a short form will be completed via a phone call on day 14, asking about the number of days they took antibiotics, other therapies, and details regarding the duration and severity of their symptoms.

## Abbreviations

AMR: antimicrobial resistance
COPD: chronic obstructive pulmonary disease
CRP: C-reactive protein
e-CRF: electronic case report form
FAIR: Findable, Accessible, Interoperable, and Reusable
GP: general practitioner
QALY: quality-adjusted life year
REDCap: research electronic data capture
RTI: respiratory tract infection
SPIRIT: Standard Protocol Items: Recommendations for Interventional Trials
t.i.d.: 3 times daily
